**Methods:**

HABVIA is a 3-year prospective controlled study to identify, implement and assess heat adaptation solutions in four low-income communities in one urban and one rural site in Ghana and South Africa, respectively. In each site, *N*=240 participants (*N*=60 per site) will be assigned to intervention or control groups. The intervention is focused on lowering the nighttime temperature of the home environment. Health and biometric data will be collected through a combination of physiological measurements, questionnaires, and biochemical measures taken at 3 time points during the hot season. Clinical outcomes include objective sleep behaviour, core body temperature, physical activity, blood pressure, blood glucose, anthropometrics, and body composition. Indoor and outdoor environmental data will be collected continuously using fixed indoor sensors and automatic weather stations. Housing and community characteristics, and socio-economic information will be collected. Quantitative comparisons will be made between intervention and control conditions using generalised linear mixed models. Qualitative data from consultive workshops will be used to assess the acceptability and feasibility of the adaptations.

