### Study aims and objectives

The HABVIA study aims to address some of the large evidence gaps in human health and wider social outcomes of heat adaptation in SSA, namely (i) the paucity of data from well-designed heat adaptation intervention trials in real-world high-vulnerability settings in the region and (ii) the absence of quantitative measurements of the health outcomes of these interventions. HABVIA aims to achieve this by identifying and implementing socially and culturally acceptable, affordable, and scalable heat adaptations for housing in low-income informal settlements in four communities in Ghana and South Africa.

Specifically, the following three objectives will be addressed:*Objective 1*. To explore the physiological response to extreme heat by quantifying the relationship between high seasonal ambient temperatures and humidity, and objectively measured health outcomes (primary: sleep; secondary: core body temperature, hydration) over three hot seasons in two rural and two urban African settings.*Objective 2*. To investigate any effects of passive-cooling interventions in lowering night-time indoor temperature and improving physical and mental health metrics, compared to controls.*Objective 3*. To determine the feasibility and social acceptability of such passive cooling adaptation interventions in climate vulnerable communities.

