#### Health data

The health data will be collected through a combination of physiological measurements, questionnaires, and biochemical measures over three measurement periods during the hot season each year. While the primary health outcome for HABVIA is sleep behaviour, other important health outcomes including core body temperature, hydration status, physical activity, blood pressure, fasting blood glucose, body composition, mental health and perception of thermal comfort will be measured.

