### Data analysis

For the statistical analysis, means and standard deviations will be presented for continuous variables; medians and interquartile ranges will be reported for continuous variables with asymmetrical distributions. Continuous variables with a small number of ordered categories, as well as all nominal variables, will be described with counts and percentages.Objective 1. The effect of ambient outdoor and indoor temperature on physiological health outcomes (primary: sleep; secondary: core body temperature, hydration) will be assessed both cross-sectionally and longitudinally using a univariable and multivariable generalized linear mixed model. For the multivariable model we will adjust for environmental conditions (humidity, cloud cover, wind speed, precipitation); health covariates (body composition, blood pressure, physical activity, glucose); participant characteristics (sex, age); household characteristics (roof and wall type; size) as well as differences between sites (country, rural vs. urban).Objective 2. The impact of the interventions will be tested in phases, first the association between intervention exposure and night-time indoor temperature, adjusting for household characteristics, site and intervention type. Secondly, the association between intervention exposure and sleep, our primary outcome as well as secondary physical and mental health outcomes. The mediating effect of night-time indoor temperature on this association will be investigated, while adjusting for the covariates described under Objective 1). In addition to this, structural equation modelling (SEM) will be used to produce a pictographic representation of a-priori determined relationships between the variables of interest. It does this by estimating path equations simultaneously allowing for the calculation of direct, indirect and total effects. For missing data, we will explore different imputation methods and run sensitivity analyses to explore whether participants lost to follow-up differ when compared to those who completed the study measurement periods.Objective 3. Qualitative data analysis will be done in parallel with the community engagement workshops and Focus Group Discussions, allowing emerging analysis to shape subsequent implementation and data collection procedures. The analysis will answer process evaluation questions and draw on various qualitative methods including but not limited to reflexive thematic analysis and codebook analysis. A qualitative analysis software (such as MAXQDA) will be used by the investigators to facilitate coding, data management, and data interpretation.

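### Objective 2 adjusts for four health variables that are themselves trial outcomes, without limiting them to pre-installation values

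*Protocol article*

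**What the plan says.** In Data analysis, the multivariable mixed model for Objective 1 adjusts for weather, "health covariates (body composition, blood pressure, physical activity, glucose"), sex and age, housing features and site differences. No time point is attached to the health variables.

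Objective 2 proceeds in steps:
- The model for night-time indoor temperature has its own short adjustment set: housing features, site and type of adaptation.
- The next step is described as "Secondly, the association between intervention exposure and sleep, our primary outcome as well as secondary physical and mental health outcomes". It names no covariates.
- The sentence after that reads "The mediating effect of night-time indoor temperature on this association will be investigated, while adjusting for the covariates described under Objective 1".

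Elsewhere the four health variables are outcomes. Health data lists "core body temperature, hydration status, physical activity, blood pressure, fasting blood glucose, body composition, mental health and perception of thermal comfort will be measured", and the abstract's Methods paragraph says "Clinical outcomes include objective sleep behaviour, core body temperature, physical activity, blood pressure, blood glucose, anthropometrics, and body composition". Study aims and objectives gives Objective 2 as the effect of "passive-cooling interventions in lowering night-time indoor temperature and improving physical and mental health metrics, compared to controls".

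Research procedures sets one season before installation (2023-2024) and two after it (2024-2025 and 2025-2026). Blood pressure and glucose are taken at the start of every measurement week, body composition once each hot season, and accelerometer activity over the same seven days as sleep.

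**The concern.** A covariate that the intervention can change is not a neutral adjustment variable. Holding it fixed removes the part of the effect that runs through it. It also opens a path through any unmeasured cause that the covariate shares with sleep. Allocation protects a contrast that is unadjusted or adjusted for pre-installation values; it does not protect one conditioned on later values. In the mediation analysis the split between direct and indirect effects loses its meaning if other variables downstream of indoor temperature are held constant.

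The text leans toward concurrent values. The model is longitudinal, and the same list contains humidity, wind, rain and cloud, which make sense only as concurrent readings. The protocol's own background also places the variables downstream: the Introduction links heat to cardiovascular strain and disturbed sleep, and poor sleep to cardiovascular disease, obesity and diabetes.

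There is also a conflict that does not depend on the size of any bias. The mediation sentence covers the secondary physical outcomes as well as sleep. Read literally, when blood pressure, glucose, activity or body composition is the outcome, it is also on the covariate list.

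**Working it through.** The plan states no figure for this adjustment, so there is none to reproduce. The only yardstick is in Sample size calculation: 11.6 minutes of sleep for 4.3 °C. No standard deviation for sleep is given, so every other input below is an assumption.

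**Formula.** In a linear model with a covariate scaled to unit SD,

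adjusted effect = total effect − a × b, with b = ρ × SD(sleep),

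where a is the effect of allocation on the covariate (in SDs) and ρ is the within-arm correlation of covariate and sleep.

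**Range**, for a from 0.1 to 0.3, ρ from 0.1 to 0.5 and sleep SD from 40 to 90 min:

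| a | ρ | SD (min) | a × ρ × SD (min) | Share of 11.6 |
|---|---|---|---|---|
| 0 | any | any | 0 | 0% |
| 0.1 | 0.1 | 40 | 0.4 | 3% |
| 0.2 | 0.3 | 60 | 3.6 | 31% |
| 0.3 | 0.5 | 90 | 13.5 | 116% |

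**Simulation of the middle case** (2,000,000 records; true effect 11.6 min; covariate and sleep share an unmeasured cause):
- unadjusted: 11.7 min
- adjusted for the baseline value: 11.7 min
- adjusted for the post-intervention value: 8.1 min (formula: 11.6 − 3.6 = 8.0)
- adjusted for both: 9.3 min
- adjusted for the post-intervention value when allocation does not move it: 11.8 min

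Adding the baseline value beside the later one therefore does not repair the estimate. The small excess over 11.6 is simulation error.

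**Direction.** Suppose a = 0.3 and 20% of the effect runs through the covariate. That part is 0.2 × 11.6 = 2.32 min, a slope of 2.32 / 0.3 = 7.73 min per SD. Let an unmeasured common cause act by 0.5 SD on the covariate and 20 min on sleep, which adds 0.5 × 20 = 10 min per SD.
- Common cause acting in the same direction on both: 11.6 − 0.3 × (7.73 + 10) = 6.3 min.
- Sign on sleep reversed: 11.6 − 0.3 × (7.73 − 10) = 12.3 min.

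The estimate can fall below or rise above the true value.

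**The case against.** The strongest reply is that the article never says post-intervention values will be used. All four variables are also measured in 2023-2024, before installation, and the choice of time point could sit in an analysis plan that is not shown. Bias is zero with baseline values, or if the intervention does not move the covariate. This stands, and it makes the point conditional. It does not remove it: the article states an adjustment rule, places it in a longitudinal model beside concurrent covariates, and applies it to variables it also calls outcomes.

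A reader might infer that the overall intervention effect on sleep is adjusted for these variables. The text does not say so: the list is attached to the mediation sentence, and the sentence on intervention and sleep names no covariates. The planned structural equation model is also meant to give a total effect.

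A reader might also infer that the effect on sleep is certain to be understated. The sign depends on assumptions, as the 12.3-minute case shows.

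Objective 1 is an exposure-response model, so the allocation argument does not reach it. Its named outcomes do not overlap with the four covariates, and a univariable version is planned as well. Over-adjustment there is a secondary matter. That the adaptation changes roof or wall type is only a possibility, because the interventions were still to be chosen.

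**Conclusion.** The point holds in conditional form. The Objective 2 mediation analysis, and possibly the intervention-sleep model, adjusts for four declared outcomes without limiting them to values from before installation. If concurrent values are used and the intervention moves them, the adjusted, direct and indirect effects on sleep are biased. Under the assumed ranges the shift is between 0.4 and 13.5 minutes, from negligible to larger than the whole 11.6-minute yardstick. The documents support neither a particular size nor a direction. The possibility that an outcome becomes its own covariate follows from a literal reading of the list and needs no such assumptions. The documents do not show that the total effect on sleep is biased as planned.

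**What to change.** For Objective 2:
- Enter the four health covariates as pre-installation values only. Do the same for roof and wall type where the adaptation alters them.
- Keep concurrent outdoor weather, which the intervention cannot change.
- Give the total-effect model its own stated covariate set with no post-intervention health variables, and report it first, by allocated group. Study design sends dwellings where installation is infeasible to control automatically, so treat these separately from randomised ones.
- Never adjust an outcome for its own post-intervention value.
- In the mediation model, let night-time indoor temperature be the only included variable that allocation can affect.
- State a rule for participants without a 2023-2024 value, for example imputation or a missing-value indicator. Participants and enrolment allows recruitment in year 2, and Trial status has recruitment running to September 2024, after the November-March season.

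For Objective 1, show the temperature-sleep estimate with and without the concurrent health measures.

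The cost is wording in the protocol and analysis plan, with no new measurements. The small downside is missing baseline values for late enrollees. If an analysis plan already restricts these covariates to baseline, the article's text need only be aligned with it.

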#### Residential, community and sociodemographic data

Characteristics of each participant dwelling as well as the outdoor environment that might affect building temperatures (building density, landcover, nearby water bodies, trees, and other shading) will be surveyed and assessed using a combination of geospatial and ground survey data. Features of the residence that will be measured include dimensions, presence of windows and doors, materials of floors, walls, ceilings and roofs, and ventilation.

Key to the success of the heat adaptation interventions is an assessment of affordability and feasibility in local-contexts, therefore comprehensive socio-economic and demographic information will be collected and considered in the evaluation. A study-specific demographic and socio-economic survey which is currently being used in the ongoing studies, and has been shown to be culturally appropriate, will be employed.

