## Discussion

Despite high vulnerability to heat-related health risk, few robust evaluations of the environmental, health and socio-economic outcomes of heat adaptations in real-world settings have been done in Africa. Indicating a dire need for reliable heat-health data and heat adaptations that are acceptable and feasible in local contexts. By addressing these gaps using extensive physiological measures, linked to environmental changes, the knowledge generated through HABVIA may help to inform policy to support the effective implementation of heat adaptations in sub-Saharan African settings, where they are sorely needed.

The controlled trial described in this protocol will explore whether passive cooling interventions impact on indoor ambient temperatures, particularly at night, and the extent to which they affect sleep quality and subsequent health outcomes. The limitations of this study include blinding issues, as it is not feasible to blind either participants or researchers to the intervention due to the highly consultive nature of the research as well as potential selection bias due to the leveraging of on-going cohorts. The study design is otherwise optimized for both internal and external validity by staggering monitoring periods, measuring potential confounders across health, climate and infrastructure, and by comparing group differences at both the cross-sectional and longitudinal endpoints.

As global warming progresses so will the need to build local capacity to respond and adapt to heat-related health issues in Africa. HABVIA aims to contribute to this by providing a multidisciplinary platform for climate-health research, education, and policy. In addition, the study’s commitment to community engagement for the design and implementation of the intervention, and the resulting mixed-methods approach, will allow for in-depth interpretation of the intervention outcomes and improve relevance and acceptability. Ultimately, the impact of these interventions will depend on uptake, by using locally sourced materials and generating site specific climate and social data that considers baseline health profiles, where pre-existing conditions may make people more vulnerable to heat stress, HABVIA is working towards tailored solutions for multi-vulnerable communities. This can also provide a framework for intervention development in future climate-related studies.

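### The listed covariates for Objective 1 and the mediation include no socio-economic measure, leaving the between-household indoor-temperature effect open to residual confounding of unknown size

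*Protocol article*

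**What the plan says.** In the protocol article, Data analysis, Objective 1 concerns temperature as an exposure: "The effect of ambient outdoor and indoor temperature on physiological health outcomes (primary: sleep; secondary: core body temperature, hydration) will be assessed both cross-sectionally and". The sentence goes on to a longitudinal analysis as well, with univariable and multivariable generalised linear mixed models. The multivariable set is enumerated. It begins "we will adjust for environmental conditions (humidity, cloud cover, wind speed, precipitation); health covariates (body composition, blood pressure, physical activity, glucose" and continues "participant characteristics (sex, age); household characteristics (roof and wall type; size) as well as differences between sites (country, rural vs. urban". For Objective 2 the same set is carried forward: "The mediating effect of night-time indoor temperature on this association will be investigated, while adjusting for the covariates described under Objective 1".

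The section on residential, community and sociodemographic data says "comprehensive socio-economic and demographic information will be collected and considered in the evaluation". The reason it gives is the assessment of affordability and local feasibility, and it names no model. The instrument is described as follows: "A study-specific demographic and socio-economic survey which is currently being used in the ongoing studies". Neither its items nor its timing is given.

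The Discussion bases validity partly on "measuring potential confounders across health, climate and infrastructure".

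**The concern.** Adjustment is not left open here. The article commits to a list detailed enough to name cloud cover and wall type, and socio-economic position is not on it even though the study collects such data.

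This matters only where randomisation gives no protection. Indoor temperature is observed, not assigned, in Objective 1. In the mediation the arm is randomised but the mediator is not, so the temperature-to-sleep step needs its own confounders in the model. If better-off households within a site have cooler bedrooms and also sleep differently for other reasons, the slope absorbs part of that difference, and the split into direct and indirect effects moves with it. The Background gives some ground for the first link: it ties amplified heat exposure to low-income settlements, inadequately cooled housing and manual labour.

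**Working it through.** **1. The passages side by side.**

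| Domain | Listed for adjustment (Data analysis) | Collected elsewhere in the article |
|---|---|---|
| Environment | humidity, cloud cover, wind, precipitation | yes |
| Health | body composition, blood pressure, physical activity, glucose | yes |
| Participant | sex, age | yes |
| Household | roof, wall, size | yes |
| Site | country, rural/urban | yes |
| Socio-economic | none | yes, by survey |

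**2. The plan's own yardstick.** Sample size calculation: 11.6 min per 4.3 °C, so 11.6/4.3 = 2.70 min/°C.

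**3. Bias in a between-household slope.** Bias = b × r / SD(T). Here b is the sleep effect per SD of socio-economic position, r is its correlation with indoor temperature after the listed covariates, and SD(T) is the remaining SD of home temperature. The documents give none of these, so all are assumed. With SD(T) = 2 °C, the entries are min/°C (% of 2.70):

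| b (min per SD) | r = 0 | r = 0.1 | r = 0.2 | r = 0.3 |
|---|---|---|---|---|
| 5 | 0 (0%) | 0.25 (9%) | 0.50 (19%) | 0.75 (28%) |
| 10 | 0 (0%) | 0.50 (19%) | 1.00 (37%) | 1.50 (56%) |
| 15 | 0 (0%) | 0.75 (28%) | 1.50 (56%) | 2.25 (83%) |

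The largest cell becomes 15 × 0.3/1 = 4.5 (167%) if SD(T) is 1 °C, and 15 × 0.3/3 = 1.5 (56%) if it is 3 °C. A second parametrisation uses two correlations and a sleep SD of 60 min, again with SD(T) = 2 °C. It gives 0.2 × 0.1 × 60/2 = 0.6 (22%) and 0.4 × 0.2 × 60/2 = 2.4 (89%).

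**4. Mediation.** Assume a randomised arm lowers temperature by 2 °C, the true slope is −2.70 min/°C and the direct effect is 0. The total effect is then (−2) × (−2.70) = 5.4 min. Suppose also that better-off homes are cooler and sleep longer. Omitting the measure gives a slope of −2.70 − b × r/2 and a direct effect of 5.4 + 2 × that slope. For r = 0.3 and b = 15 these are −4.95 and 5.4 − 9.9 = −4.5. A simulation with 240 participants, 4,000 replicates and a residual sleep SD of 50 min agrees:

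| r, b | Slope, omitted | Direct, omitted | Slope, adjusted | Direct, adjusted | Total |
|---|---|---|---|---|---|
| 0, 10 | −2.71 | −0.13 | −2.71 | −0.14 | 5.30 |
| 0.1, 5 | −3.01 | −0.50 | −2.77 | −0.02 | 5.52 |
| 0.2, 10 | −3.73 | −2.05 | −2.71 | −0.01 | 5.39 |
| 0.3, 15 | −4.97 | −4.42 | −2.72 | 0.12 | 5.51 |

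The total effect stays near 5.4 throughout. Only its split moves.

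**5. Longitudinal model.** A random-intercept fit gives the between-home slope the weight k/(1+k), where k = within variance/(within variance + n × between variance). This takes temperature variance as equal between and within homes.

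- 54 nights (6 nights × 3 weeks × 3 seasons), assumed sleep SDs of 50 between and 70 within: k = 4900/(4900 + 54 × 2500) = 0.035, weight 0.034.
- Nine single readings (3 × 3), assumed intraclass correlation 0.3: k = 0.7/(0.7 + 9 × 0.3) = 0.206, weight 0.171.

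Applied to the 0.6 to 2.4 range, 0.6 × 0.034 = 0.02 and 2.4 × 0.171 = 0.41 min/°C survive, about 1% to 15% of 2.70.

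**The case against.** The strongest reply is that confounding is not shown. No section says that household socio-economic position affects sleep. The Background reports only that the temperature-sleep association was stronger in low-income countries, which is effect modification at country level. All four sites are low-income communities, which narrows the variation. Roof and wall type, size, site and physical activity are partial proxies, and size could even be read as household size, which would touch on crowding. The promise to consider socio-economic data does not confine them to affordability, and the Discussion phrase is a summary of what is measured, not an adjustment set. Objective 1 is exploratory. All of this stands, and it limits the claim to a risk.

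It does not remove the point. Proxies leave a remainder, the word considered names no model, and the enumerated list omits the measure. An unseen analysis plan could add it, but the article would then need to match.

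A reader might infer more than the documents support in three places:

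- **That the indoor-temperature effect is confounded throughout Objective 1.** The link to sleep is not documented, and the longitudinal contrasts are largely spared.
- **That the arm comparison is biased by this omission.** Randomisation covers it. The assignment of infeasible homes to control is an exception, but a separate problem.
- **That the structural equation model also lacks the measure.** Its paths are said to be set a priori but are not listed, so nothing can be concluded.

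**Conclusion.** The point holds as a risk of residual confounding in two analyses: the cross-sectional, between-household temperature-sleep effect and the temperature-to-outcome step of the mediation. The omission is plain from the text. Its consequence is not measurable from the documents. At an assumed home-temperature SD of 2 °C the bias spans 0% to roughly 80–90% of the 2.7 min/°C planning slope, and a smaller SD would raise the upper end. The sign shown in the mediation illustration follows from the assumed directions and would reverse if one of them did. The percentages illustrate possible size and do not estimate it.

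**What to change.** Add one pre-specified socio-economic measure to the Objective 1 multivariable model and to the temperature-to-outcome model of the mediation. An asset or income index, education or occupation would serve, depending on what the survey holds. A value taken before the intervention is preferable, since the intervention cannot have altered it. The sponsor should confirm the survey's items and timing, because the article states neither. Then align the sociodemographic data section with Data analysis, so that both say whether and where the measure enters, or give the reason for leaving it out.

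The cost is a sentence in each section and a few degrees of freedom among about 240 participants (4 sites × 60). If the survey contains a suitable item, no new data are needed. Settling this before analysis also avoids choosing covariates after seeing results.
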